	**INTERVENTIONS**:					
	***Personalized digital therapeutic (intervention) group***					
	***Control group***					
	**ASSESSMENTS**:					
***7***	***Complication***		X	X	X	X
***8***	***Hb, albumin***	X ^1)^			X	X
***9***	***CT (visceral fat, muscle mass)***	X ^1)^			X	X
***10***	***Body composition***	X	X	X	X	X
***11***	***EORCT-QLQ-C30***	X	X	X	X	X
***12***	***EORCT-QLQ-CR29***	X	X	X	X	X
***13***	***MNA***	X	X	X	X	X
***14***	***IPAQ-SF***		X	X	X	X
***15***	***Grip strength***	X	X	X	X	X
***16***	***30 s chair stands test***		X	X	X	X
***17***	***2 min walk test***		X	X	X	X
***18***	^***a***^ ***LARS***		X	X	X	X
***19***	^***b***^ ***Satisfaction questionnaire***				X	

*CT*: computed tomography, *EORCT-QLQ*: European Organization for Research and Treatment of Cancer-Quality of life Questionnaire, *MNA*: Mini Nutritional Assessment, *IPAQ-SF*: International Physical Activity Questionnaire-Short Form, *LARS*: Low Anterior Resection Syndrome Score Questionnaire

^a^ Rectal cancer without ileostomy and colostomy.

^b^ Digital therapeutic group only.

^1)^ Tests analyzed within previous 6 months from the baseline can be collected.

### Primary outcome

The primary objective of this study is to determine the effect of mobile application and wearable smart band in the management of prognostic factors in colorectal cancer patients. Therefore, the primary outcome would be the skeletal muscle mass increment in the intervention group compared to the control group in 12 months from the baseline, measured using the bio impedance analysis.

### Secondary outcomes

The secondary objectives of our study are quality of life, body function and composition, and pain intensity over time.

The quality of life will be evaluated using the European Organization for Research and Treatment of Cancer-Quality of life Questionnaire (EORCT-QLQ-C30 and CR29). EORTC QLQ-C30 is composed of functional, symptom, and global quality of life domain. The quality-of-life scale uses a modified 7-point linear analog scale. All other items are scored on a 4-point categorical scale, ranging from 1 “not at all” to 4 “very much” [10]. The EORTC QLQ-CR29 is designed to complement the C30 questionnaire as a tumor-specific questionnaire for patients with colorectal cancer. It is composed of function and symptom domains [11, 12]. High overall quality-of-life, high functional domain score, and low symptom domain score correlates with high quality of life.

International physical activity questionnaire-short form (IPAQ-SF) is divided into vigorous activity, moderate activity, walking, and lying down to evaluate the amount of activity in the last seven days. The participants are also asked to define the number of min and days spent performing a specific activity category [13].

Mini nutritional assessment (MNA) defines nutritional status. It is divided into several domains for anthropometric assessment (weight, height, and weight and appetite loss) [14]. The total score is 30 points, < 17 points indicates malnutrition, 17–23.5 points indicate risk of malnutrition, and 24–30 points is considered normal.

Physical fitness is evaluated using the grip strength test, 30-sec chair stand test (CST), and 2-min walk test (2MWT). Grip strength is assessed using a hand-held dynamometer (microFET® Digital HandGRIP Dynamometer, Hoggan Scientific LLC, USA). The patients are asked to use the maximal hand grip power (kg). The patients repeat this three times for three seconds, and the average of the results will be recorded [15]. The CST is used to evaluate the strength of the lower extremities by assessing the maximal total number of repetitions of standing up to a chair that the person could achieve in 30 s. Participant is instructed to stand up and sit down fully at their maximal speed for 30 Sects. [16, 17]. The 2MWT is used to examine the cardiorespiratory endurance of the participants. It will be performed in a 15.2-m hallway. The patients will be asked to walk at their maximal speed for 2 min and the total distance they walked will be measured [18].

The abdomen and pelvis will be analyzed using computed tomography (CT). To measure muscle mass and visceral fat, we will analyze the cross-sectional area in a single CT slice at the height of the third lumbar vertebra [19].

Rectal cancer patients without ileostomy or colostomy would be evaluated for defecation function by Low Anterior Resection Syndrome Score (LARS) questionnaire. Patients are categorized into three groups: no LARS (0–20), minor LARS (21–29), and major LARS (30–42) [20, 21].

The pain intensity for the past week will be evaluated by a 11-point Numeric Rating Scale (NRS) [22] with 0 and 10 representing “no pain” and “the worst possible pain”, respectively. Participants will answer about an average and the worst perceived pain intensity score.

Additionally, the intervention group will undergo a general assessment with e-health literacy at baseline and the self-developed satisfaction questionnaire for mobile application and Internet of Things device after 6 months. The eHealth Literacy Scale (eHEALS) is designed to assess consumer’s perceived skills at using information technology for health and to aid in determining the applicability of eHealth programs for individual consumers. The eHEALS has 10 items, where items 1 and 2 are supplementary. Eight questions assess eHealth literacy on a 5-point Likert scale, in which a higher score indicates higher literacy [23].

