**Methods:**

This study is a prospective, multi-center, single-blinded, two-armed, randomized controlled trial. The study aims to recruit 324 patients from three hospitals. Patients will be randomly allocated to two groups for one year of rehabilitation, starting immediately after the operation: a digital healthcare system rehabilitation (intervention) group and a conventional education-based rehabilitation (control) group. The primary objective of this protocol is to clarify the effect of digital healthcare system rehabilitation on skeletal muscle mass increment in patients with colorectal cancer. The secondary outcomes would be the improvement in quality of life measured by EORTC QLQ C30 and CR29, enhanced physical fitness level measured by grip strength test, 30-sec chair stand test and 2-min walk test, increased physical activity measured by IPAQ-SF, alleviated pain intensity, decreased severity of the LARS, weight, and fat mass. These measurements will be held on enrollment and at 1, 3, 6 and 12 months thereafter.

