### Randomization, allocation, and blinding

We used blocked randomization with randomly selected block sizes (block size: 3 and 6). This study is an open study; therefore, the name of the group is not blinded. Owing to the nature of the intervention, the participant and evaluator can recognize which intervention has been assigned to the participant. After randomly allocating patients into two groups with a 1 (control group): 2 (intervention group) ratio, baseline assessment will be performed.

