### Outcome measures

Outcomes will be assessed at baseline and at 1-, 3-, 6-, and 12-month follow-ups. Outcome measures will be assessed by clinical research coordinator and summary of baseline screening, assessment, and follow-up during study visits is described in Table 2.

**Table 2 Tab2:** Summary of baseline screening, assessment, and follow-up during study visits

		STUDY PERIOD				
		Post-allocation				
TIMEPOINT		*Post op* *(± 1w)*	*1-month* *(± 2w)*	*3-month* *(± 1 m)*	*6-month* *(± 2 m)*	*12-month* *(± 2 m)*

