### Sample size calculation

Based on a previous study [24], the sample size was calculated with effect size of 0.35 (moderate level), 80% of power, and allocation ratio 1 (control group): 2 (intervention group) using the G-power 3.1.9.2. The results showed that the number of intervention and control group participants were at least 195 and 97, respectively. Considering the drop-out rate (10%), total number of participants was 324 (216 of intervention group and 108 of control group). We will enroll competitively participants to reach target sample size.

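### The open-evaluator statement exempts no outcome, so L3 CT muscle and visceral fat areas may be read with knowledge of the arm although stored images are easily masked

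*Protocol article*

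**What the plan says.** All references are to the Protocol article.

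- **Secondary outcomes**, on CT muscle mass and visceral fat: "we will analyze the cross-sectional area in a single CT slice at the height of the third lumbar vertebra". No reader is named, and nothing is said for or against masking.
- **Randomization, allocation, and blinding**: "This study is an open study; therefore, the name of the group is not blinded", followed by "Owing to the nature of the intervention, the participant and evaluator can recognize which intervention has been assigned to the participant". No outcome is excepted.
- **Outcome measures**: "Outcome measures will be assessed by clinical research coordinator". Table 2 in that section lists CT among the assessments, at baseline, 6 months and 12 months. Its footnote on the baseline CT reads: "Tests analyzed within previous 6 months from the baseline can be collected".
- **Primary outcome**: skeletal muscle mass change over 12 months, "measured using the bio impedance analysis". CT is not the primary measure.
- **Abstract, Methods**: "This study is a prospective, multi-center, single-blinded, two-armed, randomized controlled trial". Who is blinded is not said.

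**The concern.** The article gives a single reason for leaving evaluators unmasked, and that reason depends on contact with the patient. Someone who tests grip, supervises a chair-stand test or hands over a questionnaire can see a wrist band or hear about the app. Someone who measures an L3 slice on a saved file sees neither, unless the file is labelled with identity or arm. The general statement therefore reaches an outcome to which its own justification does not apply.

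This matters because choosing the slice and separating muscle from visceral fat can involve judgement. If the reader knows the arm, a small systematic shift in one direction is possible, and enrolling more patients does not reduce it. CT is also the only measure of muscle mass in Table 2 apart from body composition; grip strength and chair stands measure performance and depend on effort. In an open trial with a bioimpedance primary outcome, a CT result read without knowledge of arm would be useful supporting evidence. Read with knowledge of arm, it is open to the same doubt as the outcome it would support.

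**Working it through.** The point rests on the text, so the statements are set side by side first.

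1. *Scope of the evaluator statement.* The blinding section covers the evaluator without qualification. The section on outcome measures assigns outcomes to the coordinator, and Table 2 includes CT. Together these put CT inside the open rule by default. The Interventions section adds that health care professionals can view individual app use, so the arm is visible to at least some staff.
2. *Does the reason carry over?* For face-to-face tests and questionnaires, yes. For a stored image, no: neither app nor band is visible on it, and the file can be coded before it is measured.
3. *Does the document say that CT readers know the arm?* No. The CT paragraph is silent. What follows from steps 1 and 2 is that they *may* know it.
4. *Is the label consistent?* The Abstract says single-blinded. The Methods say open, and say that both participant and evaluator can tell the arm. Nobody is identified as masked.

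**Effect on the design figures.** Stated inputs (Sample size calculation; Statistical analysis): effect size 0.35, power 80%, control:intervention 1:2, significance level 5%. Sidedness is not stated; two-sided is assumed.

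- Control n = (1 + 1/2) × (1.960 + 0.842)² / 0.35² = 1.5 × 7.85 / 0.1225 ≈ 96.1, rounded up to 97. Intervention = 2 × 97 = 194, against the stated 97 and 195.
- The exact t-test power at 97 and 195 is 0.802. A one-sided test would need only 76 and 152, so the plan's figures are two-sided.
- Dropout: (195 + 97) / 0.90 = 292 / 0.90 = 324.4, against the stated 324 (216 + 108).

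The sample size reproduces to within rounding. How CT is read enters none of these formulas, so masked reading changes neither N, alpha nor power.

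**Size of a reading bias.** The documents give no L3 area, reader error or SD of CT change, so nothing can be derived from them. As an illustration only, with every input assumed: L3 muscle area 130 cm², arm-dependent shift 1–2% (1.3–2.6 cm²), SD of 12-month change 8–12 cm². Standardized bias = shift / SD:

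| Shift | SD 12 cm² | SD 8 cm² |
|---|---|---|
| 1.3 cm² | 0.11 | 0.16 |
| 2.6 cm² | 0.22 | 0.33 |

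With no arm-dependent shift, for example under largely automated measurement, the value is 0. The table shows what a shift would do if there were one; it is not evidence that there is one.

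**Interval covered.** Bioimpedance baseline is post-operative (±1 week), so its change spans a nominal 12 months. A CT baseline up to 6 months older gives a nominal CT interval of up to 12 + 6 = 18 months, which may include the operation itself.

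**The case against.** The strongest reply is that this is silence in a condensed article. Who reads scans and how files are coded usually belong to the full protocol or an imaging procedure. The evaluator sentence is permissive and most naturally describes people who meet the patient. The single-blinded label might even refer to a masked CT reader.

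Part of this stands. A reader might infer that CT readers do know the arm, or that masking was deliberately given up; no sentence says either. But the article is not merely silent. It states a general rule with a reason, exempts nothing, and assigns outcomes to the coordinator. If a masked CT reader was intended, the blinding section as written contradicts that and needs correcting in any case.

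Three further objections succeed and limit the point:

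- *CT as the only muscle measure that could be protected.* Not supported. Bioimpedance is a device reading and could be taken by someone not told the arm, although a participant might disclose it or be seen wearing the band. CT is the easiest to mask, not the only candidate.
- *Masked CT as independent confirmation of the primary result.* Too strong. The article gives CT no such role, and the CT and bioimpedance changes may cover different periods, which masking does not mend.
- *Masking at no cost.* Not supported. Files have to be coded and some scans may need re-reading.

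**Conclusion.** The point holds in a limited form. As written, the CT muscle and visceral fat areas fall under a statement that evaluators can tell the arm, and the reason given does not fit a stored image. The bias this allows is avoidable.

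Its size is unknown. A reader might set the illustrative upper value of 0.33 SD beside the planning effect of 0.35 and conclude that reading bias could mimic the whole effect. The documents do not support that: every input to the 0.33 is assumed, it pairs the largest shift with the smallest SD, and the 0.35 was used to size a trial whose primary outcome is bioimpedance, not CT.

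The consequence is confined to a secondary measure and to the weight it can bear as support for the primary result. The change is still worth making because it removes a possible bias cheaply. The conclusion assumes that no document outside this article already provides for masked reading; if one does, only the wording needs correcting.

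**What to change.** 1. In the blinding section, restrict the sentence about evaluators being able to tell the arm to face-to-face assessments.
2. In the CT paragraph under Secondary outcomes, state that images are coded before measurement and read without knowledge of arm, and of visit where feasible, with the L3 areas locked before unmasking. Visit masking may be incomplete, because a baseline scan may predate surgery; arm masking is unaffected.
3. Reconcile both with the single-blinded label in the Abstract: either say who is masked and for which outcomes, or drop the label.
4. If the masked CT result is reported beside the bioimpedance result, present it as supportive only. Note that the baseline CT may be up to 6 months old and may not span the same interval.

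The cost is a small amount of work to code image files and to re-read any scans already measured unmasked. The same scans and the same reader can be used. Sample size, alpha, power and the primary analysis stay as they are.

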### Sample size calculation

Based on a previous study [24], the sample size was calculated with effect size of 0.35 (moderate level), 80% of power, and allocation ratio 1 (control group): 2 (intervention group) using the G-power 3.1.9.2. The results showed that the number of intervention and control group participants were at least 195 and 97, respectively. Considering the drop-out rate (10%), total number of participants was 324 (216 of intervention group and 108 of control group). We will enroll competitively participants to reach target sample size.

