## Methods

### Study design

This protocol will be a prospective multi-centered two-armed randomized controlled trial. The study design meets SPIRIT guidelines [9]. The SPIRIT Checklist are attached as Additional file 1. Colorectal cancer patients will be recruited from three university hospitals in South Korea (Samsung Medical Center, Korea University Anam Hospital, and Seoul St. Mary’s Hospital). The enrolled participants will be randomly allocated to either the digital therapeutic or control group. Regardless of group allocation, all patients will receive conventional education and usual care in hospital. Patients who undergo colostomy will receive colostomy care by hospital staffs. Furthermore, patients who underwent low anterior resection surgery will receive education of the pelvic floor muscle rehabilitation by a physical therapist, 2–4 weeks after surgery. The flow diagram of the study protocol is shown in Fig. 1.

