### Statistical analysis

All data will be analyzed using IBM SPSS Statistics version 28.0.1 (Armonk, New York, USA) and a significance level of 5% will be set with a 95% confidence interval. Patient demographics will be calculated using descriptive statistics. Kolmogorov–Smirnov test will be performed to assess the distribution of data. To compare baselines between the two groups, a student’s t-test and chi-squared test will be conducted. In case the randomization is not balanced, the baseline difference will be corrected through multivariate logistic regression and analyzed. To compare the mean difference, if the primary outcome (skeletal muscle mass) data in both groups are found to be normally distributed, we will perform an independent t-test. Missing data will be handled depending on the distribution of data after study completion. To investigate the effects of the interventions and differences between groups for secondary outcomes, a mixed effects model or generalized estimating equations will be conducted, with one between-subject factor (group) and one within-subject factor (evaluation time).

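### The stated analyses omit hospital in a three-hospital trial: unbiased, but at a small cost in precision, or a conservative test if randomisation was stratified by hospital

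*Protocol article*

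**What the plan says.** All places are in the Methods of the protocol article.

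- **Study design:** three university hospitals recruit, and individual participants are allocated to one arm or the other. On background care: "Regardless of group allocation, all patients will receive conventional education and usual care in hospital".
- **Randomization, allocation, and blinding:** "We used blocked randomization with randomly selected block sizes (block size: 3 and 6", in a 1:2 ratio. Stratification by hospital is not mentioned.
- **Sample size calculation:** "We will enroll competitively participants to reach target sample size". No quota per hospital is given.
- **Statistical analysis:** if the data are normally distributed, the primary outcome is compared by an independent t-test. The secondary outcomes use a mixed effects model or GEE, "with one between-subject factor (group) and one within-subject factor (evaluation time". Adjustment is foreseen only if the arms turn out unbalanced. It would be by logistic regression, and hospital is not named.

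**The concern.** In a multicentre trial, hospital is a known source of variation in outcome. Here the article chooses analyses that ignore it. An independent t-test cannot carry a hospital term, and the secondary models are fixed at a single between-subject factor. The conditional adjustment route does not fill the gap: it depends on observed imbalance, does not name hospital, and uses a method for binary outcomes although muscle mass is continuous.

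What is at stake is efficiency. The planned evaluable sample gives almost exactly 80% power, so precision that the design already offers is worth keeping. The loss takes one of two forms, depending on whether the list was stratified:

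- **Not stratified:** the hospital mix can differ between arms by chance, and the analysis does not remove that noise.
- **Stratified:** the design has already removed the noise from the estimate, but the t-test still counts it in the standard error.

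**Working it through.** **Inputs from the article.**

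- Planning assumptions (Sample size calculation): "the sample size was calculated with effect size of 0.35 (moderate level), 80% of power, and allocation ratio 1 (control group): 2 (intervention group".
- Test level (Statistical analysis): "a significance level of 5% will be set with a 95% confidence interval".
- Evaluable patients (Sample size calculation): 195 on intervention and 97 controls.
- Enrolled patients (same section): "Considering the drop-out rate (10%), total number of participants was 324 (216 of intervention group and 108 of control group".

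**Assumed input.** The article does not give the share of outcome variance lying between hospitals (call it ρ). Values of 0, 2, 5, 10 and 20% were examined, with patients split across hospitals equally or 70/20/10.

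**1. The plan's own figure.** With a two-sided 5% level, d = 0.35, 80% power and a 1:2 ratio, the calculation gives 97 controls and 194 intervention patients, against 97 and 195 stated. Exact power at 97/195 is 80.2%. Inflating 292 by 1/(1 − 0.10) gives 324.4, or 325 when rounded up, against 324 stated. The plan's figure is reproduced, and this point does not affect it.

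**2. Standard error with and without hospital** (total SD = 1, 195 and 97 evaluable).

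- Without hospital: √(1/195 + 1/97) = 0.1242.
- With hospital: 0.1242 × √(1 − ρ).
- Approximate power: Φ(0.35/SE − 1.96).

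The formula was checked by simulating 292 evaluable patients in three hospitals, individually randomised 2:1 in blocks of 3 and 6, not stratified by hospital (2,000 runs per setting at d = 0.35).

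| ρ (assumed) | SE with hospital | Formula power, without → with | Simulated, equal hospitals | Simulated, 70/20/10 |
|---|---|---|---|---|
| 2% | 0.1230 | 80.4 → 81.2% | 79.7 → 80.2% | 81.3 → 82.1% |
| 5% | 0.1211 | 80.4 → 82.4% | 80.7 → 82.1% | 80.2 → 82.1% |
| 10% | 0.1179 | 80.4 → 84.4% | 80.0 → 82.8% | 80.5 → 84.2% |
| 20% | 0.1111 | 80.4 → 88.3% | 81.0 → 88.2% | 80.7 → 88.6% |

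The simulated gain is 1.4 to 3.7 points at ρ of 5 to 10%, and 7.2 to 7.9 points at 20%. With ρ = 0 nothing material is gained or lost (differences of 0.2 to 0.3 points).

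**3. Bias and type I error, not stratified.** The average error of the estimate was at most 0.005 SD in every setting, with or without the hospital term. With ρ of 2 to 20%, type I error without the term was 4.4 to 5.6% (4,000 null runs per setting). The unadjusted test is therefore valid.

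**4. Type I error, stratified.** The true standard error is already 0.1242 × √(1 − ρ), but the t-test reports about 0.1242. The effective critical value is 1.96/√(1 − ρ).

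- ρ = 10%: 2.07, a two-sided level of 3.9%. Simulated: 4.1% and 3.7%.
- ρ = 20%: 2.19, a two-sided level of 2.8%. Simulated: 2.8% and 2.6%.

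With hospital in the model, the simulated level at these shares was 4.4 to 5.1%.

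**5. Size of the chance imbalance, not stratified.** For a hospital supplying one third of patients (assumed), the difference in its share between arms of 216 and 108 has SD √[(1/3)(2/3)(1/216 + 1/108)] = 0.0556. If that hospital differs from the others by 0.5 to 1.0 SD (assumed), a typical shift (1 SD of imbalance) is 0.028 to 0.056 SD. Total sampling error is √(1/216 + 1/108) = 0.118 SD. The shift is a component of that figure: at 0.5 SD, the between-hospital variance is 0.25 × 2/9 = 0.0556, and 0.0556 × (1/216 + 1/108) = 0.00077 = 0.028².

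**The case against.** The strongest objection is that the stated analysis is valid without hospital. Allocation is by individual, so each hospital is expected to contribute both arms in the same ratio, and the shared background care shifts both arms alike. This stands, and the simulation agrees with it.

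A reader might still infer that differences in care between hospitals distort the treatment comparison, or that competitive enrolment lets them in. The article does not support either reading. Competitive enrolment changes how many patients each hospital supplies, not the expected split between arms within it. The article also does not say that usual care differs between hospitals, nor that it is standardised.

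A reader might also take the 95% limit of chance imbalance, 1.96 × 0.0556 = 0.109, multiply it by an assumed hospital difference of 0.5 to 1.0 SD, and report a shift of 0.054 to 0.109 SD, or 16 to 31% of the planned 0.35. That figure pairs an extreme imbalance with a difference found nowhere in the article. It also describes variation that the t-test's standard error already includes (step 5).

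Two further objections stand in part. First, the primary outcome is change from baseline, so stable differences between hospitals in patient level or bioimpedance calibration largely cancel; this makes the lower values of ρ more plausible. Second, stratification factors and covariates are often left to a fuller document, so silence on stratification is not itself a fault. But the article does not leave the analysis open: it names a test with no covariates and fixes the between-subject factors at one.

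**Conclusion.** The point holds as a minor one about precision. The stated analyses leave hospital out. The treatment estimate is unbiased in expectation, the test does not exceed its nominal level beyond simulation error, and the sample size is unaffected.

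If randomisation was not stratified by hospital, the loss is about 1 to 4 points of power at an assumed 5 to 10% between-hospital variance, and 7 to 8 points at an assumed 20%. If it was stratified, the unadjusted test is conservative, with type I error of about 4% at 10% and 2.7% at 20%. If hospitals do not differ in 12-month change, nothing is lost. The article gives no figure for between-hospital variance, so these sizes are conditional on the assumed range.

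**What to change.** Before outcome data are examined, replace the independent t-test with a linear model for 12-month change in skeletal muscle mass, with group and hospital (three levels, fixed) as factors. Add hospital as a fixed factor to each secondary mixed or GEE model. State whether the randomisation list was stratified by hospital, since this decides which of the two consequences applies; the model is the same either way.

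The cost is 2 degrees of freedom (290 to 288 with 292 evaluable patients). Hospital is already recorded, and sample size, recruitment and visits do not change. The term should be fixed in advance, because adding it after the results are seen would be open to challenge.
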